### Follow-up

Follow-up will be conducted for 36 months after treatment administration.

Patients prospectively enrolled within the consortium and treated by VT-ART will undergo ICD interrogations for up to 36 months after enrollment.

After a blanking period of 3 months, regular ICD interrogations [with intracardiac electrogram (EGM) storage of VT/VF or appropriate shock or ATP] will be prospectively collected for patients treated by VT-ART at 6, 9, 12, 18, 24, 30, and 36 months after the VT-ART procedure.

The ICD interrogation will collect the events along the last 3 months ahead of each follow-up evaluation.

Patients prospectively enrolled within the consortium and treated by RFA will undergo the same follow-up schedule if possible according to the clinical patient’s need and compliance.

Patient data retrospectively collected within the consortium and treated by either RFA or VT-ART will be retrospectively extracted at the same time points of prospective follow-up.

The final analysis will be performed only for patients with available data for the mentioned time points, either retrospectively or prospectively collected.

Quality of life will be assessed before the procedure (for prospectively enrolled patients candidate to VT-ART and RFA) and at 3, 6, and 12 months after therapy. Improvement in the patient’s quality of life will be assessed compared to the pre-treatment period using the SF36 scale.

Patient follow-up will thus, briefly, include:

•ICD interrogation (with EGM storage of VT/VF) at 6, 9, 12, 18, 24, 30, and 36 months from treatment.•A total of 12-lead ECG at 3, 6, and 12 months.•Echocardiography at 3, 6, and 12 months.•QoL assessment using the SF36 scale (7) will be performed at 3, 6, and 12 months for patients undergoing VT-ART.•QoL assessment using the SF36 scale will be performed at 6 months for patients undergoing RFA.

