## Outcome measures

The primary outcome is investigating the difference in overall cardiovascular survival among the group undergoing VT-ART and the one not exposed to the innovative procedure.

The primary efficacy endpoint is a statistically significant difference in overall cardiovascular survival between the group undergoing VT-ART and the one not exposed to the innovative procedure; this will be defined in months and calculated from the time of the last procedure (represented by the last RFA for the control group and VT-ART for the innovative one, respectively).

The secondary outcome is evaluating the difference in ventricular event-free (referred to VT/VF, appropriate shock or ATP as recorded by the ICD) survival after the last procedure between the two groups (i.e., the single or last RFA in the control group and VT-ART in the innovative group). The respective endpoint is a statistically significant difference in ventricular event-free survival (in months) after the last procedure between the two groups.

An additional secondary aim is to evaluate the reduction in the number of VT episodes compared to the pre-treatment period between the two dynamic cohorts that will be investigated.

Ventricular tachycardia recurrence will be defined as evidence of monomorphic VT at ICD interrogation (either self-limiting or terminated by appropriate shock therapy or ATP). The number of VT episodes, defined as VT burden, in the 3 months before and after the procedure will then be compared.

The respective secondary endpoint will be evaluated facing 3 months before the last procedure (i.e., either RFA or VT-ART) and 3 months after.

We did set a blanking period after VT-ART before evaluate the effect on VT burden; in a recent study by Kautzner et al., the authors supported the pre-clinical theorem of myocardial apoptosis (up to 3 months post-stereotactic ablation) followed by a creation of fibrotic lesion (6–9 months post-stereotactic ablation) in the irradiated region (5). Consequently, we propose a 3-month-blanking period after the procedure.

Since a blanking period of 3 months after the procedure will be applied, the secondary endpoint will evaluate the number of VT episodes interval accounted for the last 3 months before the procedure and of the 3–6 months after it.

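### The 3-month ICD look-back is shorter than the 6-month visit spacing after month 12, so half of that time is uncollected and event-free survival to month 36 is overstated

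*Protocol article*

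**What the plan says.** All references are to the protocol article.

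- **Follow-up, duration:** "Follow-up will be conducted for 36 months after treatment administration".
- **Follow-up, visits:** after the blanking period, ICD data on VT/VF, appropriate shocks and ATP are collected "at 6, 9, 12, 18, 24, 30, and 36 months after the VT-ART procedure". The closing list of the section repeats the schedule: "ICD interrogation (with EGM storage of VT/VF) at 6, 9, 12, 18, 24, 30, and 36 months from treatment".
- **Follow-up, look-back:** "The ICD interrogation will collect the events along the last 3 months ahead of each follow-up evaluation".
- **Follow-up, other patients:** retrospective cases from either arm are extracted at the same time points. Prospective RFA patients follow the schedule where clinical need and compliance allow. The final analysis is limited to patients with data at these time points.
- **Outcome measures:** the first secondary outcome is freedom from VT/VF, appropriate shock or ATP as recorded by the ICD. "The respective endpoint is a statistically significant difference in ventricular event-free survival (in months) after the last procedure between the two groups".
- **Blanking:** Outcome measures introduces the 3-month blanking in order to assess VT burden. Follow-up mentions it without tying it to an endpoint: "After a blanking period of 3 months, regular ICD interrogations". The definition of event-free survival does not mention it.

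**The concern.** A time-to-first-event endpoint needs continuous ascertainment from its time zero. Here the look-back equals the visit interval only up to month 12. After that it is half the interval.

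Take a patient whose first episode is in month 13. If there is no further episode, that patient is recorded as event-free to month 36. If another episode occurs in month 16, the event is dated to month 16. Both errors lengthen event-free time.

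This is the trial's only time-to-event comparison of arrhythmia control. A written look-back rule that leaves gaps is a stated rule, not a detail left to a fuller document. It matters early in the study because episodes not extracted at the time may be hard to recover later.

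**Working it through.** **Coverage, from the article's own figures**

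Inputs: visits at t = 6, 9, 12, 18, 24, 30, 36; look-back 3 months; follow-up 36 months. The collected window at each visit is (t − 3, t].

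| Visit | Collected | Gap since previous collected window |
|---|---|---|
| 6 | 3-6 | 0-3 |
| 9 | 6-9 | none |
| 12 | 9-12 | none |
| 18 | 15-18 | 12-15 |
| 24 | 21-24 | 18-21 |
| 30 | 27-30 | 24-27 |
| 36 | 33-36 | 30-33 |

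- Collected: 7 × 3 = 21 months.
- Uncollected from the procedure: 36 − 21 = 15 of 36 months (42%).
- If months 0-3 are blanked for this endpoint: 12 of 33 months (36%).
- After month 12: 12 of 24 months (50%) under either reading.
- Continuous coverage: months 3-12 only.

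**Size of the overstatement, on assumed event rates**

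The article gives no event rate, so the figures below are illustrations.

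*Model A: rates vary between patients.* Each patient has a constant rate drawn from a gamma distribution with shape 0.5 and mean m per year (both assumed), and episodes recur. The probability of no episode in t years is (1 + m·t/0.5)^(−0.5). True event-free survival at month 36 uses t = 3. The recorded value uses t = 21/12 = 1.75.

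| m per year | True: t = 3 | Recorded: t = 1.75 | Overstatement |
|---|---|---|---|
| 1 | 7^(−0.5) = 0.378 | 4.5^(−0.5) = 0.471 | 9 points |
| 2 | 13^(−0.5) = 0.277 | 8^(−0.5) = 0.354 | 8 points |
| 4 | 25^(−0.5) = 0.200 | 15^(−0.5) = 0.258 | 6 points |

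These count months 0-3 as missed. The share of patients with an episode in those months is 1 − (1 + m·0.25/0.5)^(−0.5), which is 18% at m = 1 and 42% at m = 4.

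If months 0-3 are blanked by design, the true value uses t = 33/12 = 2.75: 6.5^(−0.5) = 0.392, 12^(−0.5) = 0.289 and 23^(−0.5) = 0.209. The overstatement is then about 8, 6 and 5 points.

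*Model B: one constant rate for all patients.* With an assumed median M months to first episode and recurrence at the same rate, the true value is 0.5^(36/M) and the recorded value is 0.5^(21/M).

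| M (months) | True | Recorded | Overstatement |
|---|---|---|---|
| 6 | 0.016 | 0.088 | 7 points |
| 12 | 0.125 | 0.297 | 17 points |
| 24 | 0.354 | 0.545 | 19 points |
| 36 | 0.500 | 0.667 | 17 points |

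If episodes did not recur at all, the recorded value at M = 12 would be about 49%. In simulation under Model B, 20-34% of first episodes after month 3, and 52-59% of those after month 12, fall in an uncollected window. The second share exceeds one half because each 6-month cycle begins with its gap.

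**Effect on the comparison.** Identical gaps in both arms do not cancel. Under Model B, medians of 24 and 12 months differ truly by 0.354 − 0.125 = 0.229 and are recorded as 0.545 − 0.297 = 0.248. Medians of 36 and 24 months differ truly by 0.500 − 0.354 = 0.146 and are recorded as 0.667 − 0.545 = 0.122. The direction of the distortion is not fixed.

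**The case against.** **The look-back sentence may be a counting rule.** It could describe the unit for VT burden per visit rather than a limit on what is recorded, since the device stores episodes and the endpoint is defined by what it recorded. The case report form is not shown. This tempers certainty that data will be lost. However, the sentence is the only statement of what an interrogation collects, and nothing else in the article says that episodes between windows are captured.

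**Event-free survival cannot be measured at all.** A reader might infer this, but the article does not support it. Months 3-12 are covered without a break.

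**All 15 months are lost by mistake.** This also goes too far. Three of them are a declared blanking period. Its stated purpose is VT burden, so its scope for event-free survival is open; on the blanking reading the gap is 12 of 33 months.

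**The VT-burden window is contradictory.** One sentence reads "The respective secondary endpoint will be evaluated facing 3 months before the last procedure (i.e., either RFA or VT-ART) and 3 months after", and the Sample size section mentions 3-month burden. But Outcome measures goes on to apply the blanking and settles on 3-6 months after the procedure, and the abstract gives the 4th to 6th month. The conflict is largely resolved in the text; what remains is untidy wording.

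**The gaps favour one arm.** The looser schedule applies only to prospective RFA patients. Retrospective cases in both arms use the same time points, and analysis requires data at those points. Unequal ascertainment is possible, but the article does not show its direction or size.

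**Conclusion.** The point stands in a limited form. As written, the look-back leaves 12 of the 24 months after month 12 uncollected, and no other statement in the article repairs this. Event-free survival to month 36 is overstated by about 6-9 percentage points under Model A with months 0-3 counted as missed, and by about 5-8 points if those months are blanked. Model B gives larger values in most cases. The coverage counts follow from the article; the percentage points rest on assumed rates and could be higher or lower.

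The damage is confined to one secondary endpoint. Cardiovascular survival, the primary endpoint, does not depend on ICD windows, and the months 4-6 VT burden lies inside the first collected window. For that reason this is a change that should be made, not one on which the trial's main conclusion depends.

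**What to change.** 1. In Follow-up, replace the look-back sentence so that each interrogation collects all stored VT/VF, ATP and shock episodes, with dates, since the previous interrogation, and since the procedure at the first one. Apply this in both arms and, where records allow, to retrospective cases.
2. In Outcome measures, state once whether event-free survival starts at the procedure or after the 3-month blanking, identically in both arms.
3. As a minor tidy-up, reconcile the remaining 3-months-after wording in Outcome measures and the 3-month burden in Sample size with the stated months 4-6 window.

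With the first change, 0 of 36 months are uncollected; if collection begins after blanking, only those 3 months are. The cost is protocol and case report form wording, with the same interrogations. Some older device records may be incomplete, especially for retrospective cases. Those patients should be censored at their last continuously covered date.

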#### Sample size

The calculation of the sample size considered followed assumptions:

-A total of 95% confidence level;-The drop-out rate of 10%;-Expected difference between the two treatments for 3-month and 6-month VT burden in terms of overall response rates: 20% higher in arm including VT-ART compared to the control group;-Power of 80%.

To improve clinically adequate balancing, we will enroll two matching paired patients in the group not undergoing VT-ART for each patient who undergoes VT-ART in a 2:1 ratio, favoring a larger proportion of patients not undergoing the innovative procedure (i.e., VT-ART).

Under these hypotheses, to detect a 20% improvement in the VT burden control rate in the VT-ART group vs. the control group, we calculated the sample size (in a 2:1 ratio) upon enrolling 149 patients: 100 in the non-exposed control group and 49 in the VT-ART group. Progressively, on a multicentric basis supervised by the promoting center in the VT-ART consortium, for each VT-ART patient enrollment, a matched pair patient profile according to the predefined features will be shared with the consortium to enroll two similar patients who have not undergone VT-ART. For enrollment into the control group, recruitment of clinical cases from retrospective case series within the multicentric consortium will also be allowed, with the only condition to be not earlier than 5 years from the enrollment of the matched pair patient in the VT-ART group (to avoid the possible influence of a too early approach for standard procedures).

All statistical analyses will be performed using SPSS^®^ version 25.0 software (©Copyright IBM Corporation 1994, 2017).

Due to the potential difficulty of enrolling the patients through the complete match of all matching factors, a protocol rule will be applied through patient’s collection.

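### ICD interrogation is fixed for prospective VT-ART patients but conditional for prospective RFA controls, so the ICD-based secondary endpoints are ascertained differently in the two groups, with a bias of undetermined direction

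*Protocol article*

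**What the plan says.** All the rules at issue stand in the Follow-up section of the protocol article.

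- Prospective VT-ART patients: interrogations "will be prospectively collected for patients treated by VT-ART at 6, 9, 12, 18, 24, 30, and 36 months after the VT-ART procedure", with no condition attached.
- Prospective RFA controls: patients "treated by RFA will undergo the same follow-up schedule if possible according to the clinical" need and compliance of the patient.
- Reach of each interrogation: "The ICD interrogation will collect the events along the last 3 months ahead of each follow-up evaluation".
- Retrospective patients of either group: their data "will be retrospectively extracted at the same time points of prospective follow-up".
- Analysis set: "The final analysis will be performed only for patients with available data for the mentioned time points".

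The control group may mix both kinds of patient. Under Sample size, "recruitment of clinical cases from retrospective case series within the multicentric consortium will also be allowed".

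Under Outcome measures, two secondary endpoints rest on the device. Ventricular event-free survival counts VT/VF, appropriate shocks and ATP that the ICD records. VT burden counts monomorphic VT found when the ICD is interrogated, including self-limiting episodes, in the 3 months before the procedure and in months 3 to 6 after it. The primary endpoint is cardiovascular survival. The sample size is calculated on VT burden control.

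**The concern.** For a VT-ART patient, the calendar decides whether the device is read. For a prospective control, clinical need and compliance decide, and both can be related to arrhythmia. A control with shocks has a reason to be seen. A control who is well, or who has only silent self-limiting VT or ATP, may not. A frail control may also fail to attend because of being frail.

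The two other rules make a missed visit matter more. With a 3-month reach, the next visit does not collect what the missed one would have shown. With an analysis restricted to patients who have data, a control with a missed visit may leave the comparison altogether. Unequal detection then becomes unequal selection.

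At stake is whether a difference between groups in event-free survival or VT burden reflects the treatment or the surveillance. This is a rule for collecting data, so no later analysis can recover a log that was never downloaded.

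**Working it through.** The plan gives no attendance or detection rate, so it has no figure of its own to reproduce on this point. The total of 149 patients does not enter the check. Every attendance and event rate below is an assumption.

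**1. What a missed visit loses.** From the stated dates and the 3-month look-back:

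- Visits at 6, 9 and 12 months cover months 3–12.
- Visits at 18, 24, 30 and 36 months cover months 15–18, 21–24, 27–30 and 33–36.
- Coverage is 7 × 3 = 21 of the 36 − 3 = 33 months after blanking.
- No two windows overlap. The post-procedure burden window, months 3–6, is covered by the 6-month visit alone; the 9-month visit collects months 6–9.

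**2. Selection under the available-data rule (prospective controls).** Let e be the true event-free share, f the attendance of event-free controls and a the attendance of controls with events. Treat one interrogation as deciding who is analysed.

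Apparent event-free share = e·f / [e·f + (1 − e)·a]

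| e | f | a | Calculation | Apparent share | Error (points) |
|---|---|---|---|---|---|
| 0.40 | 0.60 | 0.90 | 0.24 / (0.24 + 0.54) | 30.8% | −9.2 |
| 0.30 | 0.75 | 0.90 | 0.225 / (0.225 + 0.63) | 26.3% | −3.7 |
| 0.50 | 0.60 | 0.90 | 0.30 / (0.30 + 0.45) | 40.0% | −10.0 |
| 0.40 | 0.90 | 0.60 | 0.36 / (0.36 + 0.36) | 50.0% | +10.0 |

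In the first three rows attendance follows need, controls look worse than they are, and the bias favours VT-ART. The last row exchanges the two attendance rates of the first, as would happen if sicker controls complied less. Controls then look better than they are. The sign follows from the attendance assumption.

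**3. Dilution by retrospective controls.** Suppose one third of controls are prospective and the retrospective ones are unaffected. Take 100 controls with e = 0.40.

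- Need-driven attendance: prospective analysed 33.3 × 0.78 = 26, of whom 8 are event-free; retrospective 66.7, of whom 26.7 are event-free. Apparent share = 34.7 / 92.7 = 37.4%, an understatement of 2.6 points.
- Attendance exchanged: prospective analysed 33.3 × 0.72 = 24, of whom 12 are event-free. Apparent share = 38.7 / 90.7 = 42.6%, an overstatement of 2.6 points.

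**4. The other possible handling: an unseen window counted as no event.** The plan does not state this; it is shown only to bound the direction. Let q be control attendance, unrelated to outcome, with VT-ART fully observed.

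- VT burden, true control rates of 50% (control) and 70% (VT-ART). Observed control-group rate = 1 − 0.50·q = 55%, 60% and 65% at q = 0.9, 0.8 and 0.7. The true 20-point difference shows as 15, 10 and 5 points.
- Event-free survival, same event process in both groups, constant rate, median 12 months. Chance of an event in a 3-month window = 1 − 2^(−3/12) = 0.159. Apparent 36-month event-free share = (1 − 0.159·q)^7, about 30% at q = 1 (VT-ART), and about 34%, 39% and 50% at q = 0.9, 0.8 and 0.6 (controls).

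This handling works against VT-ART.

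**The case against.** The strongest reply has five parts.

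- **Intended schedule.** The closing list in Follow-up gives the interrogation dates without naming a group, although its quality-of-life items do distinguish groups. One schedule for all therefore seems intended, with an open concession to practice in an observational study. That is a fair reading of intent, but the list does not withdraw the condition on RFA patients.
- **Device memory.** An ICD records between visits, so a missed visit need not lose an event. That would hold if the log were read back to the previous download. The 3-month look-back rule, as written, prevents it.
- **Missing visits.** Their handling may be set out in an analysis plan that is not shown. This stands as far as scoring goes: nothing in the article says that an unseen interval counts as event-free. It does not cover the collection rule or the available-data rule, which the article does state.
- **VT-ART is not exempt.** Retrospective VT-ART patients are admitted and can also lack data, and the available-data rule applies to both groups. This stands. The explicit contrast is between prospectively enrolled patients. Retrospective data come from existing records, so extraction at the same nominal dates does not by itself restore symmetry.
- **Size and sign.** A reader might infer that the bias favours VT-ART and, at 9.2 points, takes up nearly half of the 20-point target. The documents support neither. The sign is assumed, the sentence covers only prospective controls, and the 20 points concern VT burden response, which is not an event-free share.

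**Conclusion.** The point holds as a difference in ascertainment. For prospectively enrolled patients, the article fixes device interrogation in one group and makes it conditional in the other, on grounds that may be related to outcome. The short look-back and the available-data rule then keep a missed visit from being made good. The endpoints affected are ventricular event-free survival and VT burden; both are secondary, but the sample size rests on the second.

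The direction is not determined. Need-driven attendance with the available-data rule favours VT-ART. Poor compliance among sicker controls, or unseen events treated as absent, works against it. The size is not determined either: under the assumed rates the apparent event-free share of prospective controls moves from 40% to anywhere between 30.8% and 50%, and by about 2.6 points either way in the whole control group if only a third are prospective and the rest are unaffected.

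A reader might also infer that the primary result is biased in the same way. Cardiovascular survival is not detected by ICD, so its ascertainment does not depend on these visits. Whether the available-data rule would also restrict the survival analysis is a separate question about the analysis set.

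This is an improvement that should be made because it is cheap; it does not invalidate the design.

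**What to change.** In Follow-up:

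1. Give prospectively enrolled RFA controls the same fixed interrogation dates as VT-ART patients, and delete the condition on need and compliance.
2. Replace the 3-month look-back sentence. Take events in both groups from the dated device log, read in clinic or remotely, over the whole interval since the previous download. A late download can then still supply months 3–6 and the other windows. Without this change the common schedule does not help when a visit is missed.
3. Apply the same log-based rule to retrospective patients of either group, and flag interrogations that were triggered by need.
4. Report the number of interrogations and the months of log coverage by group.

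The cost is amendment wording and some additional device downloads in prospective controls. An ICD is an inclusion criterion (Table 1), so no new equipment is needed.

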Multicenter recruitment will allow for a more precise assessment of the effects of VT-ART, with the aim of demonstrating that implementing such a procedure is both feasible and safe among centers. Moreover, it will increase the chances to recruit patients with profiles matching the ones in the arm undergone VT-ART.

A standardized data collection has been defined for data regarding both VT-ART and RFA.

The trial will thus both collect prospective and retrospective data about VT-ART (following the predefined standardized data collection). Prospective data collection will be applied within the consortium for the patients referred to VT-ART after the beginning of the trial; retrospective data collection will be allowed for the VT-ART procedure delivered before the formal start of the trial if the data required by the predefined standardized data collection are available for defining the primary and secondary endpoint (see following sections). Similarly, prospective and retrospective data collection will be allowed for data about conventional treatment (i.e., RFA).

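### As worded, the final-analysis rule keeps only patients with data at the listed follow-up times, with no exception for death, although the primary endpoint is cardiovascular survival.

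*Protocol article*

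**What the plan says.** The Follow-up section of the protocol article sets the horizon: "Follow-up will be conducted for 36 months after treatment administration". ICD interrogations for VT-ART patients are collected "at 6, 9, 12, 18, 24, 30, and 36 months after the VT-ART procedure". Retrospective records for either treatment "will be retrospectively extracted at the same time points of prospective follow-up". Prospectively enrolled RFA patients "will undergo the same follow-up schedule if possible according to the clinical patient’s need and compliance". The rule for the analysis set comes directly after these statements: "The final analysis will be performed only for patients with available data for the mentioned time points, either retrospectively or prospectively collected".

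Outcome measures defines what is compared: "The primary efficacy endpoint is a statistically significant difference in overall cardiovascular survival between the group undergoing VT-ART and the one not exposed". Survival is measured in months from the last RFA (controls) or from VT-ART.

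Two other places bear on the point. Protocol overview admits earlier VT-ART cases on a data condition: "retrospective data collection will be allowed for the VT-ART procedure delivered before the formal start of the trial if the data required" by the standard data collection is available to define the primary and secondary endpoints. Toxicity evaluation says that all-cause mortality will be reported. Neither changes the set of patients in the final analysis, and no section exempts patients who die or are censored.

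**The concern.** A patient who dies at month 10 has no interrogation at month 12 or later. If data at the listed times are a condition for entering the final analysis, that patient is left out because of the very event the primary endpoint counts. Membership of the analysis set then depends on surviving follow-up, and the survival comparison is made among survivors. Patients who are alive but have shorter follow-up are lost in the same way, although a survival analysis could use their time at risk.

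The loss need not be equal in the two groups. VT-ART patients have a fixed schedule. Prospective RFA patients follow it subject to clinical need and compliance, so whether their data exist may depend on how they are doing. Dropping members of matched sets also disturbs the planned two-to-one matching.

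**Working it through.** **Reading the rule.** The protocol offers no figure to reproduce here: it states no death rate and no survival difference. The 149 patients (100 control, 49 VT-ART) were sized on a 20% difference in VT-burden control, and the point does not depend on that calculation.

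Three readings of the sentence are possible:

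1. Data are needed at all the listed times, up to month 36. Every patient who dies before month 36 fails the condition.
2. Data are needed only at the first visit, month 6. Every patient who dies before month 6 fails.
3. Data are needed at the times reached before death or last contact. No death is lost.

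The first is the plain reading: the sentence follows the full list, says *only*, and carries no qualifier. The third is harmless but is not stated anywhere.

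**Inputs.** Group sizes of 100 and 49 are from Sample size. The visit times are from Follow-up. Annual mortality *a* is an assumption, taken as 15% with a range of 10% to 20%, constant over time and equal in both groups.

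**Deaths by 36 months**, 1 − (1 − a)³:

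| a | Proportion dead | Of 100 controls | Of 49 VT-ART |
|---|---|---|---|
| 10% | 1 − 0.729 = 27.1% | 27 | 13 |
| 15% | 1 − 0.614 = 38.6% | 39 | 19 |
| 20% | 1 − 0.512 = 48.8% | 49 | 24 |

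Under reading 1 all of these patients leave the analysis. The number of primary events before month 36 is then zero at any value of *a*.

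**Deaths before month 6**, 1 − (1 − a)^0.5. At 15% this is 1 − 0.922 = 7.8%, or about 8 controls and 4 VT-ART patients. As a share of the 36-month deaths it is 7.8 / 38.6 = 20%. This is the loss under reading 2. If the 12-month visit were also required, the loss would be 15.0 / 38.6 = 39%.

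**Effect on a real difference.** Suppose 36-month survival is 70% in controls and 80% with VT-ART (again an assumption). Deaths are 100 × 0.30 = 30 and 49 × 0.20 = 9.8, about 40 in all. Reading 1 keeps 70 and 39.2 patients. The ratio of controls to VT-ART falls from 100 / 49 = 2.04 to 70 / 39.2 = 1.79. Observed 36-month survival becomes 100% in both groups, and the 10-point difference disappears.

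**The case against.** The strongest reply is that the sentence does not say *every* time point and does not say that deaths are excluded. Both are inferences. For a survival endpoint, a patient known to have died at month 10 has a known status at later times, so data could be called available. The closing words about retrospective or prospective collection suggest that the authors mainly meant to admit both sources. A rule that empties the primary endpoint of events is unlikely to have been intended, and an article may leave censoring rules to a fuller document. This stands to the extent that one cannot claim as fact that deaths will be removed. It does not rescue the sentence, which is a stated restriction with no exception. An analyst who follows it as written gets a wrong analysis set.

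Two stronger inferences are not supported:

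- A reader might conclude that the Protocol overview condition also selects retrospective VT-ART cases on their outcome. It concerns completeness of records, and a recorded cardiovascular death does define the primary endpoint. The remaining gap is narrow: a patient who died before or during months 4 to 6 may lack the VT-burden data and be refused for that reason.
- A reader might conclude that early deaths, and any treatment harm behind them, would vanish from the report. Toxicity evaluation commits to reporting all adverse events and all-cause mortality. What remains is bias in the between-group comparison.

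It is also fair that the mortality rates used here are assumed. The counts illustrate size; the defect follows from the rule.

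**Conclusion.** The concern holds as a defect in a stated rule. As worded, the rule restricts the final analysis in a way that, on its plain reading, conditions cardiovascular survival on surviving to month 36. The size depends on the reading: all deaths before 36 months on the plain one, deaths before month 6 if only that visit is needed, and none if the unstated reading (visits reached before death) was meant. With assumed mortality of 10% to 20% a year, the plain reading excludes 27% to 49% of patients through death alone. At 15%, the 6-month version loses about a fifth of the 36-month deaths. Unequal loss between groups is possible, given the conditional schedule for RFA patients, but its direction and amount cannot be derived from the protocol. Because the rule governs the primary comparison, it must be changed before analysis.

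**What to change.** Replace the sentence in Follow-up with a rule on these lines:

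- **Analysis set.** All enrolled matched patients enter the survival analyses from the date of the last procedure, whatever visit data they have.
- **Cardiovascular survival.** Cardiovascular deaths are events. Non-cardiovascular death is a competing event, or is censored if that is stated in advance. Survivors are censored at last contact.
- **Ventricular event-free survival.** Death counts as an event or as a competing event. It should not be treated as uninformative censoring.
- **Visit-based secondary endpoints.** Any data-availability condition applies only here. For VT burden, state beforehand how death before month 6 is handled.

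In Protocol overview, add only that a retrospective VT-ART patient who died before completing the VT-burden window is not refused for lacking month 4 to 6 data. Requiring a full consecutive retrospective series would go further than this point needs and would not be a change of wording alone.

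Cost: revised wording, and some patients who contribute partial follow-up. No additional patients or visits are required.
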